#### Recruitment {15}

Psychotherapists will be recruited through their chambers and professional associations via e-mail newsletters, advertisements in print distributions, and events. Participating psychotherapists will receive study material for their patients.

### Assignment of interventions: allocation

#### Sequence generation {16a}

A randomization mechanism is hard coded into the online platform that hosts the intervention prior to starting recruitment.

#### Concealment mechanism {16b}

After patients complete their baseline assessment, the platform automatically randomizes them to one of the two groups.

#### Implementation {16c}

Randomization will occur at the patient level. Once patients consent to participate and provide baseline data, they are randomized to blended therapy or face-to-face therapy in a 1:1 ratio. We expect therapists to contribute at least 5 patients each. To ensure that each therapist treats patients of both groups, we will use block randomization with a block size of four to randomize patients. The randomization will be automated after the baseline assessment is completed and carried out by the platform that hosts TONI.

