### Strategies to improve adherence to interventions {11c}

Psychotherapists are informed about ways to integrate TONI into therapy and sessions in video tutorials at the beginning of the trial and in a study manual that they receive via mail. To ensure that psychotherapists invite patients to participate in the study and use TONI, they will receive a monetary compensation for the tutorials, which is paid out after including three patients, and for the usage of TONI for every patient in the blended care group. The platform automatically logs engagement with TONI. This includes numbers and duration of logins, modules/chapters assigned and completed, and messages exchanged. Patients receive e-mail notifications if a new module or assessment is available to them. Both patients and therapists also have a newsfeed on their dashboard notifying and reminding them about tasks or events.

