### Assignment of interventions: blinding

#### Who will be blinded? {17a}

Due to the nature of psychotherapeutic treatment trials, neither participants nor therapists can be blind to treatment allocation. Therefore, group allocation will be masked for the statistical analyses concerning group differences between blended and face-to-face therapy. As data on usability and usage of the intervention is only available for the blended therapy group, these measures will not be included in the masked data set. A separate data set will contain these data and will be analyzed once the analysis of group differences is finalized.

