The trial has several limitations: This study compares two active treatments, hypothesizing that blended therapy may be superior to regular psychotherapy in routine care. One of the assumptions behind this hypothesis is that patients may receive a higher treatment dosage by using additional online modules. However, the treatment dosage is dependent on whether psychotherapists actively engage with the intervention and assign modules. A strength of this is that it represents real-world behavior and as such is externally more valid. However, it may limit conclusions about the actual effect of making use of the full potential of the modules. We collect data on the usage of the modules and will add it as moderators to evaluate its possible impact on the results. Psychotherapists will also be in charge of recruiting their patients. This may constitute a bottleneck for the recruitment of patients, potentially jeopardizing recruitment rates. The recruitment procedure may limit the generalizability of the results, as psychotherapists choose which patients to invite to participate in the study. In addition, we are not conducting a cost analysis.

The present RCT investigates the superiority of blended over psychotherapy alone in routine care. The integration of online interventions like TONI that use a common therapeutic language and address therapeutic principles shared across therapeutic approaches has the potential to advance the effectiveness of psychotherapy. TONI may not only improve the effectiveness of psychotherapy in routine care but help save therapists’ resources and close treatment gaps.

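### A single published block size of four, applied within unblinded therapists who choose whom to invite, lets a therapist who keeps count deduce up to about a quarter of allocations

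*Protocol article*

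**What the plan says.** Under Implementation {16c} the protocol article sets the ratio ("they are randomized to blended therapy or face-to-face therapy in a 1:1 ratio"), the expected cluster size ("We expect therapists to contribute at least 5 patients each") and the method: "To ensure that each therapist treats patients of both groups", "we will use block randomization with a block size of four to randomize patients". No other block size is mentioned.

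Under Concealment mechanism {16b}: "After patients complete their baseline assessment, the platform automatically randomizes them to one of the two groups". Sequence generation {16a} says the mechanism is coded into the platform before recruitment starts.

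Under Who will be blinded? {17a}: "neither participants nor therapists can be blind to treatment allocation". The Discussion notes that "psychotherapists choose which patients to invite to participate in the study", and treats this as a limit on generalizability and a possible recruitment bottleneck, not as a matter of internal validity.

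Under Strategies to improve adherence {11c}, therapists are paid "for the usage of TONI for every patient in the blended care group". The assessment payment in section {18b} does not differ by arm.

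**The concern.** Permuted blocks of one small, known size become predictable to anyone who sees the earlier allocations in the same block. Here the person who sees them also decides who is invited next. Platform randomization keeps the list unreadable and the assignment unalterable. It does not stop a therapist from working out the next slot and then choosing, delaying or withholding an invitation.

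If that happened, patients in the deduced slots would differ in prognosis by arm. A therapist random intercept does not correct this, because the selection is between patients of the same therapist. With a target effect of only 0.2 SD, a modest distortion would matter.

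**Working it through.** **Inputs from the protocol article.** Block size 4, ratio 1:1, at least 5 patients per therapist (Implementation {16c}); d = 0.2, two-sided 5%, 80% power, 400 per arm, design effect 1.2, dropout factor 1.2 (Sample size {14}). Blocking within therapist is inferred from the stated purpose. Trial-wide blocks could not guarantee both arms for each therapist.

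**The plan's own figure.** A two-sample calculation gives 393 to 394 per arm, which the article rounds to 400. Then 400 × 1.2 × 1.2 × 2 = 1152, and 1152 / 5 = 230.4, so 231 therapists. The stated total reproduces. The article gives no figure for predictability.

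**Deducible allocations, block of four.** There are 6 equally likely orders. An allocation is forced once one arm's two places are used.
- Positions 1 and 2: never forced.
- Position 3: forced if the first two are alike, probability 1/3.
- Position 4: always forced.
- Per block: 0 + 0 + 1/3 + 1 = 4/3, so 33.3% over complete blocks (384 of 1152).
- At five patients (one block plus one): (4/3) / 5 = 26.7%, and 0.267 × 1152 ≈ 307.
- For 4 to 12 patients per therapist the share runs from 22% to 33%.

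**Best-guess accuracy** (always guess the arm that is behind). By position: 1/2, 2/3, 2/3, 1, then 1/2 for the fifth patient. At five patients: (0.5 + 0.667 + 0.667 + 1 + 0.5) / 5 = 66.7%. Over complete blocks: 2.833 / 4 = 70.8%. Simple randomization gives 50%.

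**Illustrative bias.** Forced slots fall equally in the two arms on average, so bias = 0.267 × g × f. Here g is the prognosis gap in SD between patients placed in deduced blended slots and those placed in deduced face-to-face slots, and f is the share of forced slots exploited in the same direction. Neither is in the documents; both are assumptions. Type I error is two-sided with 400 per arm, so SE = √(2/400) = 0.0707.

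| g (SD) | f | Bias (SD) | Type I error |
|---|---|---|---|
| 0.1 | 1 | 0.027 | about 7% |
| 0.3 | 1 | 0.080 | about 20% |
| 0.5 | 1 | 0.133 | about 47% |
| 0.1 to 0.5 | 0.1 | 0.003 to 0.013 | not computed |

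**Alternative block schemes.** Exact enumeration at five patients per therapist, with sizes equally likely and the therapist knowing the set of sizes but not the current one:

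| Sizes | Certain | Best guess | One arm only, 3 patients | One arm only, 4 patients |
|---|---|---|---|---|
| 4 | 26.7% | 66.7% | 0 | 0 |
| 4, 6 | 5.0% | 64.3% | 5.0% | 0 |
| 4, 6, 8 | 0.2% | 62.2% | 8.1% | 1.0% |

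The 8.1% is (0 + 0.100 + 0.143) / 3, the chance that the first three are alike for sizes 4, 6 and 8. The 1.0% is 0.0286 / 3, since only size 8 permits four alike.

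**The case against.** **Deducible is not known.** A reader might infer that a quarter of allocations are known before invitation. The article does not support that. It does not say therapists are told the block size; they would need to find it in print and keep count. According to Participant timeline {13}, patients receive a link or code and then sign up, consent and complete baseline themselves. Slots are therefore filled in order of completion, not invitation, and with two invitations open the therapist cannot tell who takes the forced slot. An invited patient may also decline. This stands: 26.7% is a ceiling.

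**The payment.** A reader might see a financial motive to steer better-prognosis patients into blended therapy. The payment rewards use of TONI. Over a complete block two blended places are filled whoever takes them, so placing a particular patient earns nothing extra. The payment makes the arms differ for the therapist and no more.

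**The bias range.** A reader might take 0.03 to 0.13 SD as expected bias. It assumes every forced slot is exploited, always in the same direction. Baseline PHQ-8 and GAD-7 precede randomization, and section {20c} foresees covariates, so selection on measured severity could be partly adjusted for. Selection on unmeasured traits such as motivation could not.

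**A defensible trade-off.** Blocks of four guarantee both arms from a therapist's third patient, which serves the stated aim. That is a real advantage, and any change gives up part of it.

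What survives is the opening itself. Nothing in the article varies the block size, withholds it, or considers deduction from earlier allocations.

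**Conclusion.** The point holds as a weakness of concealment, not as evidence of bias. Up to 26.7% of allocations at five patients per therapist, and 33.3% over complete blocks, can be deduced if four conditions hold: blocks run within therapist, the therapist knows the size, keeps count, and has patients complete baseline one at a time. The first follows from the stated purpose; the other three are possible but not documented. The resulting bias cannot be sized from the article. The change is recommended rather than essential: the protection is standard and cheap and concerns the primary comparison, but the harm is conditional and the current scheme serves a stated aim.

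**What to change.** **Future blocks.** For therapists not yet started, and from each active therapist's next block, keep stratification by therapist but draw block sizes at random (e.g. 4, 6 and 8) and do not disclose the current size. This nearly removes certain knowledge; a best guess is still right 62.2% of the time.

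*Cost:* a small platform change. With 4, 6 and 8 both arms are guaranteed only from the fifth patient. If that is too late, sizes 4 and 6 guarantee both arms from the fourth patient and leave 5.0% of allocations certain. The article reports recruitment from mid-June 2022, expected to end by June 2023, so only later blocks benefit.

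**Patients already randomized.** Flag the forced allocations from the recorded order: the fourth in each block, and the third after two alike. Then:
- Compare baseline PHQ-8 + GAD-7 by arm among them. Even with all 307 (about 153 per arm), the 95% interval has a half-width of about 1.96 × √(2/153) = 0.22 SD, so a null result is weak reassurance and says nothing about unmeasured prognosis.
- Add a sensitivity analysis of the primary outcome that excludes them and adjusts for baseline. Dropping 26.7% widens the standard error by roughly 1/√0.733 = 1.17, and partly predictable slots remain, so this supports the intention-to-treat analysis and does not replace it.

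*Cost:* no new data, only allocation order and baseline scores, which pass through the platform.

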### Assignment of interventions: blinding

#### Who will be blinded? {17a}

Due to the nature of psychotherapeutic treatment trials, neither participants nor therapists can be blind to treatment allocation. Therefore, group allocation will be masked for the statistical analyses concerning group differences between blended and face-to-face therapy. As data on usability and usage of the intervention is only available for the blended therapy group, these measures will not be included in the masked data set. A separate data set will contain these data and will be analyzed once the analysis of group differences is finalized.

#### Procedure for unblinding if needed {17b}

The design is open-label so unblinding for study coordinators will not occur.

### Data collection and management

#### Plans for assessment and collection of outcomes {18a}

##### Primary outcome

The primary outcome measure is mental distress, as measured by the composite score of the 7-item Generalized Anxiety Screener (GAD-7) and 8-item Patient Health Questionnaire (PHQ-8). Individually, both scales have demonstrated satisfactory validity and reliability and are widely used outcome measures in psychotherapy research [25–28]. As a composite score, the PHQ-ADS, a sum score of the GAD-7 and PHQ-9, has been found to have good convergent and construct validity as well as sensitivity to change in both anxiety and depression [29]. We do not expect deviations by using the PHQ-8 instead of the PHQ-9, since the PHQ-9 and PHQ-8 demonstrate equal diagnostic accuracy [30]. The PHQ-8 omits one of the PHQ-9’s items that assess thoughts about death or self-harm. Psychotherapists routinely monitor suicide ideation over the course of treatment. Since psychotherapists can only access their patient’s answers to the questionnaires when their patients are randomized to the blended therapy condition and we cannot ensure that psychotherapists review and follow up on their patients’ answers to questionnaires, we chose the PHQ-8 instead of the PHQ-9.

##### Secondary outcome measures

All secondary outcome measures (see Table 2) have shown satisfactory reliability and validity in previous studies. We will assess satisfaction with life with the 5-item Satisfaction with Life Scale (SWLS) [31, 32]. Physical and psychosocial functioning will be assessed with the 35-item Assessment of Quality of Life (AQoL-8D) [33]. For transdiagnostic symptoms, we will assess issues relating to eating/body image with the 8-item EDE-Q8 [34], alcohol and cannabis use with the 3-item AUDIT-C [35] and 4-item DUDIT-C [36], and sexual functioning with the 5-item Massachusetts General Hospital Sexual Functioning Questionnaire (MGH) [37]. Personality traits will be assessed with a brief version of the Personality Inventory for DSM-5 (PID5BF +) [38] and personality structure with the OPD-Structure Questionnaire Short form [39]. We will assess satisfaction with treatment with an adapted version of the 8-item Client Satisfaction Questionnaire (CSQ-8) [40, 41] and negative effects with the 20-item Negative Effects Questionnaire (NEQ) rated both by patients as well as psychotherapists [42]. Patients will also report their health care utilization with selected items of the FIMPsy [43]. Psychotherapists will rate symptoms and changes in general symptomatology using the CGI-S and CGI-C [44]. Patients and psychotherapists will rate the usability of the blended intervention with the 10-item System Usability Scale (SUS) [45]. At *t*_3_, psychotherapists will be asked to quantify the time they spent working with the online modules per month. They will also report in open-ended questions which potentials and limitations they see in applying blended care and how TONI can be improved.

##### Other measures

We will assess traumatization in childhood with the adverse childhood experiences questionnaire (ACE). Furthermore, we will assess self-efficacy with the 3-item General Self-efficacy Short Scale (ASKU) [46] and mental health self-efficacy with the 6-item Mental Health Self-Efficacy Scale (MHSES) [47]. Empowerment will be assessed with 2 open-ended questions. Patients will also rate their therapeutic agency with the 15-item Therapeutic Agency Inventory (TAI) [48]. Furthermore, they will rate their therapist’s activity and techniques with the 20-item Comparative Psychotherapy Process Scale (CPPS) [49] and facilitative skills with the 7-item common factor subscale of the Multitheoretical List of Therapeutic Interventions (MULTI) [50]. Patients and psychotherapists will rate therapeutic alliance with the 12-item Working Alliance Inventory (WAI-SR) [51]. Finally, three self-drafted items will assess expected treatment effects and the expected likelihood of dropping out at the beginning of therapy. At 6 months, patients will then also rate to what extent their symptoms changed and to what extent therapy helped them achieve these changes. For every face-to-face session, patients who receive blended therapy will report to what extent TONI was integrated into the face-to-face session and—if their psychotherapist activated this functionality—complete two rating scales, the Session Rating Scale (SRS) [52] and Outcome Rating Scale (ORS) [53]. To investigate therapist effects and patient-therapist matches, we will further assess therapist personality via the BFI-10 [54]. Patients and therapists will also rate their perceived similarity using a self-formulated item. If a psychotherapist signals that face-to-face therapy has terminated, two self-formulated items assess whether this termination can be considered a dropout and what the reasons for terminating therapy were.

#### Assessment of significant others

We will assess significant others at the beginning of treatment and at *t*_3_. Assessments of significant others will explore their expectations of treatment effects and dropout of the patient (3 self-drafted items), the perceived distress of the patient (GAD-7 and PHQ-8), their own distress (GAD-7 and PHQ-8), the consequences of their caregiving of the patient with the 31-item Involvement Evaluation Questionnaire (IEQ) [55], and perceived negative effects of treatment for the patient (NEQ). At the end of treatment, we will also ask them to rate the therapy-associated changes in terms of symptoms and their relationship (6 adapted items plus 3 open-ended questions).

#### Qualitative interviews

Ten strategically and sequentially selected psychotherapists will be invited to an in-depth semi-structured qualitative telephone interview about their experience and satisfaction with the treatment as well as perceived opportunities and limitations of the blended therapy approach. A strategic selection is applied to ensure a balanced representation of different therapeutic approaches and demographics.

Twenty strategically and sequentially selected patients will also be answering questions in an in-depth semi-structured qualitative telephone interview about their experience and satisfaction with the treatment as well as perceived opportunities and limitations of the blended therapy approach. A strategic selection is applied to ensure a balanced representation of different responder statuses, symptom severity, and demographics.

#### Plans to promote participant retention and complete follow-up {18b}

Participants will receive e-mail notifications that questionnaires are available on the TONI platform. Questionnaires will be available for 4 weeks, and patients will be reminded weekly as long as they do not complete the assessment. Participants who end or drop out from psychotherapy will still be invited to participate in the assessments. Patients and psychotherapists will receive a monetary incentive to complete assessments. Patients will receive €100 total for completing all four major assessments. Psychotherapists will receive €100 total for the completion of assessments per patient.

#### Data management {19}

Except for the qualitative interviews, all data is gathered online and will be recorded automatically. Data will be stored on a secure server. After study completion, de-identified data will be made publicly available in an Open Science Framework (OSF) repository.

#### Confidentiality {27}

Participants will register on the TONI platform with their e-mail addresses to receive reminders and recover their accounts. All data is stored on a secure platform, and personal data will be masked in the databases.

#### Plans for collection, laboratory evaluation, and storage of biological specimens for genetic or molecular analysis in this trial/future use {33}

n/a: No biological specimens will be collected.

## Statistical methods

### Statistical methods for primary and secondary outcomes {20a}

For the primary analyses, we will include data of all randomized patients (intention-to-treat (ITT) analysis). To account for the nesting of patients (level 1) in psychotherapists (level 2), the ITT effect is estimated 6 months after the start of treatment using multilevel models. In an exploratory analysis, the influence of the actual use of the online modules is analyzed. For this purpose, the extent of actual use (e.g., number of modules used) and the time of use are inserted as moderators, and conditional effects are estimated. The same analyses are repeated for the secondary outcome measures. An appropriate alpha error correction is applied to avoid alpha error accumulation for secondary outcomes (Bonferroni-Holm). Effect sizes for pre- to post-treatment and between-group comparisons for the main and secondary outcomes will be calculated to evaluate the effectiveness of the intervention. The qualitative interviews will be recorded, transcribed, and analyzed according to a qualitative content analysis by trained staff with an appropriate review of the assessment quality (inter-rater reliability).

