### Objectives {7}

This randomized controlled trial (RCT) evaluates whether providing psychotherapists access to online modules that they can integrate into psychotherapy benefits patients and psychotherapists. We hypothesize that patients in the blended therapy condition show larger reductions in symptoms over time than participants that solely receive face-to-face therapy. We hypothesize this effect to be small. We will investigate the treatments’ effects on the level of functioning, satisfaction with life, transdiagnostic symptoms, and personality. In addition, length of treatment, satisfaction with treatment, and negative effects are considered. We will investigate which moderators and mediators are relevant for treatment effects. We will also explore how psychotherapists and patients engage with the intervention and whether the extent of usage of the intervention moderates effects. In addition, qualitative interviews with psychotherapists and patients will shed light on the barriers and facilitators of the intervention. Furthermore, we will assess significant others of enrolled patients in a sub-study.

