### Intervention description {11a}

TONI is a digital toolbox comprising modules and self-tracking tools that can be used to blend Internet-based components and face-to-face psychotherapy. TONI consists of 12 transdiagnostic modules (see Table 1 for a description of the intervention components). Every module consists of two to seven chapters. Psychotherapists can individualize modules by selecting chapters and choosing which TONI components to integrate when into their treatment. Patients can also request access to modules. In addition to the modules, TONI includes several tracker tools that allow patients to track their distress, mood, activity, sleep, craving, or individual problems which they can share with their therapist. Patients can also use a diary and have access to an “emergency kit” with emergency contacts and skills to apply during a crisis. Optionally, psychotherapists can choose to communicate with their patients via the platform.

**Table 1 Tab1:** Intervention components

Module	Description of major concepts and components
Development	In chapter 1, patients learn about the biopsychosocial etiological model of distress and reflect on factors that may influence and maintain their symptoms. In chapter 2, patients reflect on their own biographical history and identify possible commonalities between fluctuations in their mental health. In chapter 3, patients develop a genogram of their family history and relations to identify intergenerational patterns that may influence them in their present.
Values and goals	In chapter 1, patients reflect on their motivation for change and identify barriers to change they have encountered in the past. Chapter 2 helps patients to identify their personal values that guide them through life. In chapter 3, patients reflect on the goals they want to work towards in therapy.
Mindfulness	In chapter 1, patients are introduced to the concept and components of mindfulness. Chapter 2 offers a selection of different internal and external mindfulness-based exercises.
Getting active	In chapter 1, patients learn about the relationship between activity and mood. In chapter 2, they reflect on which activities give them fulfillment and enjoyment. In chapter 3, they work towards implementing more activities in their everyday life.

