### Criteria for discontinuing or modifying allocated interventions {11b}

TONI automatically logs adherence and engagement with the online modules. We will report adherence and usage metrics. Therapists decide to what extent online modules are assigned and integrated based on the course of therapy. Therapists have access to certain usage metrics which allows them to monitor their patients’ platform usage (e.g., last login more than 4 weeks ago, % of modules completed) and address potential issues in in-person sessions or via the integrated messenger. In addition, therapists can monitor symptom progression and session ratings and adjust the intervention if necessary. Patients will be invited to assessments even if they drop out of therapy or discontinue working on modules.

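### Module use is planned as a moderator of the treatment effect, but it arises after randomisation and only in the blended arm, so the exploratory conditional effects would be confounded within-arm associations

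*Protocol article*

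**What the plan says.** Statistical methods for primary and secondary outcomes {20a} first sets out the intention-to-treat comparison at 6 months. It then turns to use: "In an exploratory analysis, the influence of the actual use of the online modules is analyzed". The method is that "the extent of actual use (e.g., number of modules used) and the time of use are inserted as moderators, and conditional effects are estimated". The section goes on to repeat its analyses for the secondary outcomes.

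The same intention appears twice more. Objectives {7} will explore "whether the extent of usage of the intervention moderates effects", and the Discussion states: "We collect data on the usage of the modules and will add it as moderators to evaluate its possible impact on the results".

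Four other statements bear on whether this can work:

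- Who will be blinded? {17a}: "As data on usability and usage of the intervention is only available for the blended therapy group", these measures are kept out of the masked data set and analysed separately afterwards.
- Criteria for discontinuing or modifying allocated interventions {11b}: "Therapists decide to what extent online modules are assigned and integrated based on the course of therapy".
- Intervention description {11a}: "Patients can also request access to modules".
- Discussion, limitations: "the treatment dosage is dependent on whether psychotherapists actively engage with the intervention and assign modules".

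**The concern.** A moderator of a randomised effect must have a value in both arms that assignment does not influence; usually it is a baseline characteristic. Module use fails on both counts. It exists only because a patient was assigned to TONI, and it accumulates afterwards through choices by therapist and patient that respond to how the patient is doing.

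Randomisation therefore does not protect a comparison made at a given level of use. Patients who stay in therapy, engage, or have an active therapist may use more modules and may also have done better without them. Conversely, a therapist may assign more modules to a patient who is doing badly. Patients who leave therapy are still followed up under {11b} and {18b}, so low use may also be a mark of early leaving.

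What is at stake is the trial's statement on whether the amount of use matters, for the primary outcome and, as {20a} is written, for the secondary outcomes too. If the intention-to-treat result were null, a favourable conditional effect among heavy users could be read as efficacy in those who used the modules properly. The planned analysis could not support that reading.

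**Working it through.** **The plan's own figures.** The article gives no figure for the use analysis. Its sample size (Sample size {14}) supplies the scale for the illustration below. For d = 0.2, two-sided alpha 5% and 80% power, n = 2 × (1.960 + 0.842)² / 0.2² ≈ 393 per arm, close to the stated 400. Then 400 × 1.2 × 1.2 = 576 per arm, or 1152 in total, and 1152 / 5 = 230.4, so about 231 therapists. The stated figures reproduce; the point does not depend on them.

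**Step 1: what can be estimated.** Let A be arm (1 = blended) and U be use. A standard moderator model is

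E(Y) = b0 + b1·A + b2·U + b3·A·U.

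- If U is missing in controls, they drop out and there is no treatment contrast left to moderate.
- If U = 0 in all controls, A·U = U for every patient. The design matrix with columns 1, A, U, A·U has rank 3, not 4 (checked numerically with 1152 patients, 576 per arm). So b2 and b3 cannot be separated.
- With one of the two columns removed, the matrix has rank 3 of 3 and the model can be fitted. Its single use coefficient is determined by the blended arm alone.

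The conditional effect at use u is then E(Y | A = 1, U = u) − E(Y | A = 0): blended patients who ended up at use u, against all controls rather than the controls who would have used that much.

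**Step 2: how large the confounding could be.** The documents do not say how strongly use relates to prognosis, so the following are assumptions shown as a range: outcome SD 1, correlation of 0.5 in size between prognosis and outcome, and no causal effect of assignment or use. Use is standardised within the blended arm and has correlation r with prognosis. The expected slope per SD of use is −0.5 × r (negative means fewer symptoms). One thousand simulated trials of 1152 patients, without therapist clustering or dropout, gave:

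| r (use, prognosis) | Expected slope (SD) | Simulated slope (SD) | Share with p < 0.05 |
|---|---|---|---|
| 0 | 0.00 | 0.00 | 4% |
| 0.1 | −0.05 | −0.05 | 23% |
| 0.2 | −0.10 | −0.10 | 67% |
| 0.3 | −0.15 | −0.15 | 96% |
| 0.5 | −0.25 | −0.25 | 100% |

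Hand check at r = 0.2: the standard error is about 1/√576 = 0.042, so z = 0.10/0.042 = 2.4 and P(Z > 1.96 − 2.4) = P(Z > −0.44) ≈ 0.67.

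With true effects of zero, the conditional effect at one SD above mean use equals the slope. At r = 0.2 that is 0.10 SD, or 0.10/0.20 = half the planning effect. If use instead rises with poor prognosis, the signs reverse and heavy use looks harmful.

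**Step 3: whether another section repairs it.** Section {20c} adds covariates to support the missing-at-random assumption and to gain precision; it does not address why some patients use more modules. Section {20b} defers other moderator and mediator analyses to a later stage and leaves the use analysis in {20a} as it stands.

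**The case against.** The strongest reply is that the plan already ranks this analysis as exploratory, keeps the usage data separate until the group comparison is finished, and lists therapist-dependent dosage as a limitation. All of that is true. It means that no primary estimate, error rate or sample size is touched, and a reader who infers that the trial's main conclusion is at risk goes further than the documents allow. But the limitation concerns conclusions about full use of the modules. It does not mention selection into use, and the Discussion then offers the moderator analysis as the response.

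A second reply is that the effect is not strictly unidentified. A reader might conclude from the collinearity that the model cannot be fitted at all. That is too strong: the article does not write out a model with separate use and interaction terms, and the reduced model with arm and arm × use is estimable. The defect is what the coefficient means.

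Third, the separate usage data set in {17a} is compatible with an analysis inside the blended arm, and exact model terms may properly be left to an analysis plan. That is fair. But the article speaks of moderators and conditional effects in {20a}, and of moderation or moderators again in {7} and the Discussion. A purely within-arm analysis would not deliver moderation of a between-arm effect.

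Finally, the size of any bias rests on assumptions, and its sign is open. That stands.

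**Conclusion.** The point holds as a should-fix matter confined to the exploratory use analysis. As worded, that analysis would present a non-randomised association within the blended arm as moderation of the randomised effect. This conclusion rests only on the article's statements that use exists in one arm and that therapists set it as therapy unfolds.

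The magnitude is illustrative: spurious slopes of 0.05 to 0.25 SD per SD of use for assumed use-prognosis correlations of 0.1 to 0.5, against a planning effect of 0.2. The true correlation, and whether it favours or penalises heavy use, cannot be known from the document. It should therefore not be inferred that the analysis would necessarily exaggerate benefit; it could equally hide one.

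Nor do the documents support treating an instrumental-variable analysis as the required correction. Assignment to the blended arm also brings trackers, a diary, an emergency kit and messaging ({11a}), and therapist access to questionnaire answers and session assessments ({18a}). An effect running only through module use is therefore doubtful. With one binary instrument and zero use in controls, the estimate is essentially the intention-to-treat effect divided by mean use, which does not show whether the degree of use matters.

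**What to change.** In {20a}, replace the moderator and conditional-effect wording with an analysis of extent and time of use within the blended arm only, adjusted for baseline PHQ-ADS and therapist. State that the result is a non-randomised association without causal interpretation. Apply the same wording where the analysis is repeated for secondary outcomes. Change Objectives {7} and the Discussion so that they speak of an association between use and outcome rather than moderation of effects.

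A complier-average or instrumental-variable estimate may be added as an option, provided that its exclusion restriction is stated together with the reasons for doubting it here, and that it is not presented as an answer on degree of use.

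The cost is a change of wording and one simple model on usage data that the platform already logs ({11c}). The price is interpretive: the trial can then draw no conclusion about a causal dose effect of the modules. Adjustment for baseline severity and therapist reduces confounding but does not remove it.
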